#### 12-month follow-up WB-MRI

The study will be reported by the same pair of radiologists who reported the baseline scans. The findings on the follow-up study will be compared with the baseline WB-MRI with access to all conventional imaging. The presence of changes in size of lesions evident on the baseline WB-MRI and/or resolution of lesions evident on baseline WB-MRI will be recorded. Any discrepant findings will be reviewed, and the status of these lesions will be determined in a consensus panel review.

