**Fig. 2 Fig2:**
[figure not shown]
Enhanced reference standard derivation flowchart. FN: False Negative, TP: True Positive, FP: False Positive, TN: True Negative, UK: Unknown, ADT: Androgen Deprivation Therapy

Patients will be divided into those with and without metastases evident on conventional imaging. For those with metastases (left arm of Fig. 2), concordant positive WB-MRI findings will be deemed to be true positive and discordant WB-MRI findings will be considered to be false negative.

For patients without metastases on conventional imaging (right arm of Fig. 2), clinical and biochemical follow-up together with changes between baseline and follow-up WB-MRI will be used to enhance the reference standard.

Where baseline WB-MRI was negative and concordant with conventional imaging, the presence of new lesions (at follow-up WB-MRI ± repeat routine imaging) coupled with a PSA rise over the 12-month will classify the baseline WB-MRI as false negative, i.e. disease was present but not visualised. Whereas the absence of new lesions regardless of PSA status over the 12-month follow-up period will confer baseline WB-MRI true negative status.

For positive findings on baseline WB-MRI discordant with conventional imaging, the baseline WB-MRI will be deemed true positive when a new lesion declared itself (on follow-up WB-MRI ± routine imaging) or the visualised lesion on baseline WB-MRI enlarged (on follow-up WB-MRI); and this was accompanied with a PSA rise within the 12-month follow-up period. Whereas, the baseline WB-MRI will be deemed false positive when the lesion evident at WB-MRI resolved or reduced in size at follow-up (in the absence of systemic therapy) regardless of PSA change. Lesions that resolved following systemic therapy (which is initiated in the 1-year follow-up period irrespective of negative conventional baseline imaging) with corresponding decrease in PSA will be classified as true positive.

Finally, patients with negative baseline conventional imaging with discordant lesion and PSA changes over the 12-month follow-up (i.e. lesion size/number increase without corresponding PSA increase) will be classified as unknown.

The section below describes the thresholds for PSA and lesion size changes, and they will be interpreted in the context of treatment intervention and subsequent treatment response or progression.

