## Discussion

At the time of writing, the LOCATE trial is the largest prospective multi-centre trial to compare WB-MRI with conventional imaging pathway specifically in patients with radio-recurrent prostate cancer.

The LOCATE trial will be informative because it compares comprehensive imaging pathways and takes into consideration the cost-effectiveness of each pathway. This trial will therefore provide valuable information to guide potential implementation of new imaging platforms for prostate cancer management pathways.

The results from the LOCATE trial would be relevant to the current clinical management pathway, specifically, should WB-MRI be advocated in the NHS in the setting of BCR.

The LOCATE trial design includes important features: unlike most other trials, the initial finding on WB-MRI will be validated using 1 year follow up WB-MRI scans, corroborating the findings on initial scan in the context of patient management. In this way, we minimise the potential overcalling of disease positivity by WB-MRI that could lead to an overestimated sensitivity of WB-MRI compared to conventional imaging techniques.

Additionally, and in order to define the most cost-effective imaging pathway for the health care system, we will perform an economic evaluation which includes a comprehensive set of sensitivity analyses to identify uncertainty in both clinical and economic estimates. Whilst recent trial designs incorporating WB-MRI are including health economic analysis [35–38], such information is still unavailable for prostate cancer imaging pathways.

The LOCATE study has some potential limitations. Firstly, we are using a combined biochemical/imaging follow-up to derive an enhanced reference standard against which the results of WB-MRI will be analysed. Although histopathological confirmation would have been preferable in cases where a discrepancy exists between WB-MRI and conventional imaging tests, such approach is technically challenging and ethically not feasible [39].

Secondly, whilst the qualitative and metastatic staging findings can be generalised to other imaging platforms, such generalisability would be limited in quantitative biomarker imaging analyses (heterogeneity index). However, ongoing work is being carried out to improve standardisation of quantitative MRI imaging across different platforms that could ultimately aid in generalisation of such technique [39, 40].

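### In men negative on conventional imaging, repeat WB-MRI helps set its own reference standard, so disease it misses twice is scored true negative; this mechanism raises apparent sensitivity, but the net bias is unknown

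*Protocol article*

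**What the plan says.** The rules are in the protocol article, under 'Derivation of enhanced reference standard' (the text that follows Fig. 2).

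- **Conventional imaging positive.** The patient is taken as diseased. If WB-MRI is negative, "discordant WB-MRI findings will be considered to be false negative".
- **Conventional imaging negative.** "clinical and biochemical follow-up together with changes between baseline and follow-up WB-MRI will be used to enhance the reference standard".
- **Both baseline tests negative, scored false negative.** This requires "the presence of new lesions (at follow-up WB-MRI ± repeat routine imaging) coupled with a PSA rise over the 12-month" period. Follow-up WB-MRI is the standing source of new lesions; routine imaging is marked ±.
- **Both baseline tests negative, scored true negative.** "the absence of new lesions regardless of PSA status over the 12-month follow-up period will confer baseline WB-MRI true negative status".
- **Only WB-MRI positive, scored true positive.** This requires a new lesion or enlargement together with a PSA rise, or resolution on systemic therapy with a PSA fall.
- **Lesion growth, or more lesions, without a PSA rise.** Classed as unknown.

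Under '12-month follow-up WB-MRI': "The study will be reported by the same pair of radiologists who reported the baseline scans", and the findings are "compared with the baseline WB-MRI with access to all conventional imaging". The Discussion presents the repeat scan as a design strength: "the initial finding on WB-MRI will be validated using 1 year follow up WB-MRI scans".

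**The concern.** In the conventional-negative branch the index test contributes to the truth against which it is judged. If disease is of a kind or size that WB-MRI does not show, a second WB-MRI may well not show it either, so the errors of the test and of its reference are correlated. A confirmed PSA progression cannot overturn the label, because the true-negative rule disregards PSA.

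This branch is central to the trial. The Background says that up to half of men judged free of metastases by conventional staging have micro-metastatic disease. The article fixes the rule itself, so this is not a detail left to an analysis plan. At stake are absolute WB-MRI sensitivity and specificity, and the diseased denominator shared by both tests in the primary comparison.

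**Working it through.** **Scale.** 'Sample size' gives 130 patients at 50% prevalence: 130 × 0.5 = 65 diseased and 65 not. The 130 serves here only as a scale. It cannot be confirmed, because the discordant proportion is not stated; a two-sided McNemar calculation gives 65 diseased (129 in total) if that proportion is 0.26.

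**Assumed inputs (none in the document).** Half of the diseased men, 32.5, are conventional-positive, and WB-MRI agrees in 90% of them. In the other 32.5, baseline WB-MRI sensitivity is 60%. Let r be the probability that a diseased man negative on both baseline tests still has no new lesion at 12 months.

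**Step 1: truth.** WB-MRI detects 0.9 × 32.5 + 0.6 × 32.5 = 29.25 + 19.5 = 48.75, and 48.75/65 = 75.0%. Conventional sensitivity is 32.5/65 = 50.0%. The gap is 25.0 points.

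**Step 2: the mechanism alone.** Men scored true negative despite disease: h = 0.4 × 32.5 × r = 13r. Apparent WB-MRI sensitivity = 48.75/(65 − h). Gap = (48.75 − 32.5)/(65 − h).

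| r | h | 65 − h | WB-MRI | Conventional | Gap (points) |
|---|---|---|---|---|---|
| 0.5 | 6.5 | 58.5 | 83.3% | 55.6% | 27.8 |
| 0.7 | 9.1 | 55.9 | 87.2% | 58.1% | 29.1 |
| 0.9 | 11.7 | 53.3 | 91.5% | 61.0% | 30.5 |

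The same h men are added to both numerator and denominator of specificity.

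**Step 3: a second model.** Let the tests be independent given disease, with WB-MRI sensitivity w, conventional sensitivity c, and a share m of double-negative diseased men without a new lesion at 12 months. Apparent sensitivity = w/[1 − (1 − c)(1 − w)m].

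- w = 0.70, c = 0.50: 0.727, 0.757 and 0.824 for m = 0.25, 0.5 and 1.
- w = 0.80, c = 0.60: 0.816, 0.833 and 0.870.
- If optional routine imaging exposed half of the twice-missed cases, the m = 1 values would fall to 0.757 and 0.833.

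**Step 4: the rules that act the other way, with the Step 1 inputs.** Each line adds one offset; results are for r = 0.5, 0.7 and 0.9.

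- *Conventional specificity 95%, WB-MRI negative in the false positives.* These 0.05 × 65 = 3.25 men count as diseased and as WB-MRI misses. WB-MRI: 48.75/(68.25 − h) = 78.9%, 82.4%, 86.2%. Gap: (48.75 − 35.75)/(68.25 − h) = 21.1, 22.0, 23.0 points.
- *Conventional specificity 90%.* 6.5 such men. WB-MRI: 48.75/(71.5 − h) = 75.0%, 78.1%, 81.5%. Gap: (48.75 − 39)/(71.5 − h) = 15.0, 15.6, 16.3 points.
- *Metastases arising after baseline in 10% of the 65 non-diseased men.* 6.5 men scored false negative. WB-MRI: 48.75/(71.5 − h) = 75.0%, 78.1%, 81.5%. Gap: 16.25/(71.5 − h) = 25.0, 26.0, 27.2 points.
- *30% of WB-MRI-only detections ending as unknown.* 0.3 × 19.5 = 5.85 men drop out. WB-MRI: 42.9/(59.15 − h) = 81.5%, 85.7%, 90.4%. Gap: (42.9 − 32.5)/(59.15 − h) = 19.8, 20.8, 21.9 points.

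**Step 5: offsets combined in the second model.** Take w = 0.70, c = 0.50, m of 0.5 to 1, conventional specificity 90% to 100%, WB-MRI specificity 95%, new disease in 0 to 20% of non-diseased men negative on both tests, and 0 to 30% of WB-MRI-only detections unclassified. Apparent sensitivity runs from 0.55 to 0.82 around the true 0.70. The upper end is 45.5/55.25 = 0.824. The lower end is 39.0/70.9 = 0.550: detections are 22.75 + 0.7 × 22.75 + 0.05 × 6.5 = 39.0, and the denominator is 65 − 4.875 − 6.825 + 6.5 + 0.2 × 58.5 × 0.95 = 70.9.

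**The case against.** The strongest reply is that the reference standard incorporates both tests. Every conventional positive is accepted as disease, so a conventional false positive raises conventional sensitivity and lowers that of WB-MRI. Metastases that appear after baseline are also charged to WB-MRI. This stands. A reader might infer from the true-negative rule that reported WB-MRI sensitivity is inflated overall and that its lead over conventional imaging widens; Steps 4 and 5 show that neither follows.

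A reader might also infer that a benign lesion over-read on both scans would be confirmed as metastatic. The rules do not support this. A lesion that merely persists does not qualify: enlargement or a new lesion with a PSA rise is needed, or resolution on systemic therapy with a PSA fall.

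Next, the Discussion lists the combined biochemical and imaging reference as a limitation and says histology is not feasible. That is a partial acknowledgement. The protection it claims against overestimated sensitivity concerns overcalling, which does not touch disease missed twice.

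Finally, a derivation without follow-up WB-MRI relies on routine imaging that is optional and that the Background itself calls insensitive, and a PSA rise may reflect local recurrence. This is a real weakness. It is a reason to use the second derivation as a sensitivity analysis with an unknown class, not as a replacement.

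**Conclusion.** The point holds for men negative on baseline conventional imaging. In that branch, any twice-missed disease not revealed by routine follow-up imaging is removed from the sensitivity denominator and counted as a correct negative. Taken alone, this can only raise apparent WB-MRI sensitivity: from 75% to between 83% and 91% under the Step 1 assumptions, and from 0.70 to at most 0.82, or 0.80 to at most 0.87, in the second model.

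Three limits apply. Disease seen on conventional imaging but missed by WB-MRI is still counted against WB-MRI. Routine follow-up imaging, where done, can recover some of the hidden cases, provided PSA also rises. The size and sign of the net bias, and its effect on the difference between the tests, depend on conventional specificity, new disease and unknown cases, for which the document gives no figures. Opposing biases of unknown size leave one derivation of the reference standard insufficient to carry the conclusion alone. Fig. 2 is not shown; this reading rests on the text that describes it.

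**What to change.** Keep the current derivation as primary. Before analysis starts ('Study status' says data are still being collected), pre-specify a sensitivity derivation as follows.

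1. A repeat negative WB-MRI alone does not confer true-negative status.
2. Conventional-negative men are classed from routine follow-up imaging where done, PSA by the protocol's own progression and response definitions, and clinical follow-up.
3. Men whom these do not settle are unknown, a class the plan already has. This includes men negative on both baseline tests with confirmed PSA progression and no new lesion, since the rise may come from local recurrence.
4. WB-MRI and conventional accuracy are reported under both derivations, with best- and worst-case bounds for the unknowns.
5. If the two differ materially, the conclusion is worded as sensitivity for disease that becomes visible on conventional imaging or WB-MRI by 12 months.

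No new scans are needed. The cost is more unknown men, wider intervals, and a second derivation that leans more on the comparator modalities. Disagreement between the two would show how much the result depends on the reference standard, not which version is right.

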### Reporting of trial imaging

#### Initial WB-MRI scan

The study will be reported by two experienced radiologists, blinded to all other imaging investigations, initially independently and then in consensus using a locked sequential read paradigm (LSR). The images will be reviewed for the presence of nodal (N) and metastatic (M) disease and each radiologist will record the presence/absence of disease on the study-specific proforma.

The initial WB-MRI read results will not be revealed to the clinical team. Where a significant additional/incidental finding is demonstrated this will be reported as per standard clinical practice and relayed to the clinical team.

A 1–6 Likert scale [23, 25] will be used for scoring as has been previously described for WB-MRI studies. 1 – disease definitely not present, 2 – probably not present, 3 – possibly not present, 4 – disease possibly present, 5 – probably present and 6 – definitely present.

Scoring will be conducted based on evaluation of imaging features of lymph nodes and bone metastases as indicated below in Table 2 .

**Table 2 Tab2:** Features suggestive of adverse and benign changes in both nodes and bones

	Benign features	Adverse features
Node	Lymph node <5 mm in short axis diameter (SAD) with no concerning features on DWI, T2 weighted or contrast enhanced imaging and definite benign features e.g. (i) Fatty hilum, (ii) Oval nodal morphology with clearly defined and (iii) Regular nodal border and contours.	Concerning features could be described as (i) Size above normal limit e.g. > 10 mm for most, (ii) Loss of fatty hilum, (iii) Irregular border, (iv) Asymmetric high DWI signal intensity, (v) Low T2 signal
Bone	Normal appearing bone with uniform moderate-high signal on T1 weighted imaging and low-moderate signal on T2 weighted imaging. Focal lesions demonstrating clearly incidental/benign multiparametric signal characteristics and/or location	(i) Increase in DWI high b-value signal vs. background noise. (ii) Low signal intensity on T1 and (iii) Intermediate to high signal intensity on T2 (iv) Lesional contrast enhancement

*DWI* Diffusion weighted imaging

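### In men negative on both baseline tests, growth of a lesion seen at baseline but scored as not disease is labelled true negative even with PSA progression, which slightly overstates absolute WB-MRI accuracy

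*Protocol article*

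**What the plan says.** The rules are in the protocol article, section Derivation of enhanced reference standard, in the text after Fig. 2.

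- **Both baseline tests negative.** WB-MRI becomes a false negative on "the presence of new lesions (at follow-up WB-MRI ± repeat routine imaging) coupled with a PSA rise over the 12-month". Otherwise: "Whereas the absence of new lesions regardless of PSA status over the 12-month follow-up period will confer baseline WB-MRI true negative status".
- **Conventional imaging negative, WB-MRI positive.** A new lesion proves disease, and so does growth: "or the visualised lesion on baseline WB-MRI enlarged (on follow-up WB-MRI); and this was accompanied with a PSA rise".
- **Unknown.** For men negative on conventional imaging, whatever their WB-MRI result, a mismatch between lesion and PSA change is set aside: "i.e. lesion size/number increase without corresponding PSA increase) will be classified as unknown".

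The list that closes the section gives the thresholds for true change. For a node this is a short-axis increase of at least 2 mm. PSA progression is a confirmed rise of at least 25% and at least 2 ng/mL.

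The section Initial WB-MRI scan uses a six-point scale whose midpoint runs "3 – possibly not present, 4 – disease possibly present". Its Table 2 lists among benign bone appearances: "Focal lesions demonstrating clearly incidental/benign multiparametric signal characteristics and/or location". The section 12-month follow-up WB-MRI has the readers record this: "The presence of changes in size of lesions evident on the baseline WB-MRI".

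**The concern.** A negative WB-MRI read need not be an empty scan. The scale and Table 2 both provide for a node or bone lesion that is seen and judged not to be disease. If that judgement was wrong, growth over 12 months with a rising PSA is the evidence most likely to show it. The both-negative branch does not use this evidence; it asks only whether a lesion is new.

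Two consequences follow. First, the reference label depends on the index reading it is meant to judge: one lesion course proves disease after one score and absence of disease after the next score down. Second, the error always runs the same way. A diseased man leaves the sensitivity denominator and enters the specificity numerator, so both WB-MRI estimates can only rise. The article makes per-patient sensitivity and specificity against this reference standard its main results.

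**Working it through.** **1. Courses in the both-negative branch, taken literally**

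| Course at 12 months | Rule that applies | Label |
|---|---|---|
| New lesion, PSA rise | false-negative rule | false negative |
| New lesion, no PSA rise | unknown rule (number increase) | unknown |
| No new lesion, no growth, any PSA | true-negative rule | true negative |
| No new lesion, visible lesion grows, PSA rise | true-negative rule only | **true negative** |
| No new lesion, visible lesion grows, no PSA rise | true-negative rule and unknown rule | **both** |

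The fourth row is the error. The fifth is a direct conflict. Together they reverse the order of evidence: growth without PSA support may be unknown, while growth with it is true negative.

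**2. An invented record**

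Conventional imaging is negative. A 6 mm node is scored 3. At 12 months it measures 11 mm, PSA has gone from 6 to 14 ng/mL (confirmed), and nothing is new.

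- Growth is 11 − 6 = 5 mm, against a threshold of 2 mm.
- The PSA rise is 8 ng/mL, or 8/6 = 133%, against thresholds of 2 ng/mL and 25%.
- Label by the stated rule: true negative. Had the node been scored 4 at baseline, the label would be true positive.

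The article gives no cut-off for a positive read. Taking 1–3 as negative and 4–6 as positive is an inference from the scale wording.

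**3. The article's own figure, used for scale**

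The section Sample size gives 130 men at 50% prevalence, so 130 × 0.5 = 65 diseased, and a 20-point difference in sensitivity. It gives no discordant proportion ψ, so 130 can be neither confirmed nor refuted. It is reproduced with an assumed ψ = 0.26 in the paired formula (two-sided 0.05, 90% power):

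n = (1.960·√0.26 + 1.282·√(0.26 − 0.04))² / 0.04 ≈ 64.04, rounded up to 65 diseased; 65/0.5 = 130.

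The point does not depend on this figure.

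**4. Size per mislabelled man**

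Assumed counts: of 65 diseased men, WB-MRI is positive in 52 (80.0%) and conventional imaging in 39 (60.0%). Of 65 men without disease, 6 are WB-MRI false positives, leaving 59 true negatives. Let k diseased men be labelled true negative.

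| k | WB-MRI sensitivity, 52/(65−k) | Conventional sensitivity, 39/(65−k) | Difference, 13/(65−k) | WB-MRI specificity, (59+k)/(65+k) |
|---|---|---|---|---|
| 0 | 80.0% | 60.0% | 20.0 points | 90.8% |
| 1 | 81.25% | 60.9% | 20.3 points | 90.9% |
| 3 | 83.9% | 62.9% | 21.0 points | 91.2% |
| 5 | 86.7% | 65.0% | 21.7 points | 91.4% |

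In general, the first such man adds S × (65/64 − 1) = S/64 to a true sensitivity S. That is 0.94, 1.09 or 1.25 points for S of 60%, 70% or 80%, or about 1 point.

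**5. Effect on the comparison with conventional imaging**

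A split that fits step 4 is: both positive 37, WB-MRI only 15, conventional only 2, neither 11 (total 65; 17/65 = 0.26). Mislabelled men come only from the last cell. The McNemar statistic, (15 − 2)²/(15 + 2) = 169/17 = 9.94, is therefore the same for every k. So is the sensitivity ratio, 52/39 = 1.33.

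**The case against.** **New may mean newly called as disease.** On this view, a lesion judged benign at baseline and reported as disease at follow-up is new. An 11 mm node exceeds the size that Table 2 gives as adverse for most nodes, so a reader might well call it disease. This makes the wording open to argument, but it does not settle the label. The adjoining paragraph lists a new lesion and an enlarged lesion as alternatives, and Table 2 applies the word lesion to benign findings. A node growing from 6 to 9 mm would meet the 2 mm threshold without passing the 10 mm limit, so on size alone this reading would not reliably rescue it.

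**The article foresees growth in this group.** The unknown rule covers men negative on both tests, and it implies that growth with a PSA rise is concordant evidence. That is a fair account of the intent. It still leaves the true-negative sentence saying the opposite.

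**A consensus panel decides lesion status, and Fig. 2 may show a growth path.** Both could soften the problem in practice. However, no link from the panel to the per-patient label is stated. Fig. 2 is not visible here; if it has such a path, figure and text need reconciling.

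**Size change is already recorded.** This stands. The follow-up section does not limit recording to lesions scored positive, so the data should largely exist.

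**The effect on the comparison is small.** This stands too. A reader might infer that the rule biases the test of WB-MRI against conventional imaging. The documents do not support that: the affected men are negative on both tests, so they never enter a discordant pair. Only the difference in percentages moves, because its denominator shrinks.

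**Conclusion.** As written, the both-negative branch mislabels growth with PSA progression as true negative and gives two labels to growth without it. Both faults are in the stated rule; they are not detail that an article would leave to a fuller document.

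The consequence is limited. With 65 diseased men, each case overstates absolute WB-MRI sensitivity by about 1 point and, on the assumed counts, specificity by about 0.1 point. The size rests on three things the article does not give: the positive cut-off (inferred), the true sensitivities and specificity (assumed), and the number of such men (unknown, probably small).

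A reader might infer a large inflation, since 5 such men would turn 80.0% into 86.7%. Nothing in the article supports a count of that order, so the table shows direction and scale and is not a forecast. The error always favours WB-MRI, and the correction is cheap, so it is worth making before the analysis.

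**What to change.** Rewrite the both-negative branch so that it matches the WB-MRI-positive branch and the unknown rule:

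- **False negative:** new lesions, or enlargement beyond the section's own thresholds of a lesion visible on baseline WB-MRI but scored as not disease, in either case with PSA progression.
- **Unknown:** either change without PSA progression.
- **True negative:** neither change.

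Bring Fig. 2 into line if it differs. State that the size-change recording at 12 months also applies to lesions scored benign at baseline.

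The cost is one clause, a line on the proforma and a few more measurements. No new scans are needed, because the follow-up study is already read against the baseline. The reported WB-MRI sensitivity may be slightly less favourable, and men with growth but no PSA rise would be unknown instead of carrying two labels. The section Study status says that data were still being collected and full analysis had not begun, so at that stage the rule could be corrected before it was applied.

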## Background

Prostate cancer (PCa) is the leading male cancer in the United Kingdom and a principal cause of cancer-related mortality with around 46,700 cases diagnosed in 2014 [1]. The incidence of PCa has increased markedly over the past 20 years and it is projected to rise by 12% between 2014 and 2035 to 233 per 100,000 males [1]. Common treatments options for localised prostate cancer are external beam radiation therapy (EBRT), brachytherapy (BRT) or radical prostatectomy [2].

However, biochemical recurrence (BCR) following radiotherapy occurs in 25% of treated men within 5 years, manifesting as a rising prostate-specific-antigen (PSA) [3]. This is strictly a biochemical diagnosis, most commonly defined as an increase in serum PSA of 2.0 ng/ mL above the nadir [4]. Once a PSA relapse has been diagnosed, it is important to determine whether the recurrence has developed at local or distant sites and hence BCR following therapy often initiates an imaging-based assessment of local and metastatic disease in patients.

Local recurrence of PCa is investigated by prostate multi-parametric magnetic resonance imaging (mp-MRI) [5] whilst metastatic disease is assessed by multi-modality imaging. The standard workup to detect PCa metastases usually includes ^99m^Tc bone scan and chest/abdomen/pelvis (CT-CAP) scan (or where available ^18^F-choline or ^68^Ga-PSMA PET-CT) [6].

The workup to exclude distant metastasis is of greatest significance as it is estimated that about half of those who develop radio-recurrent disease have distant metastases (either overt on imaging or micro-metastases) [7]. It is also believed that up to 50% of men who are considered to be free of metastases by conventional staging methods have micro-metastatic disease [8]. This is reflected in prostate cancer recurrence following EBRT or BRT, where biochemical relapse commonly precedes clinical detection of metastases by an average of 7–8 years [9].

Earlier detection of metastatic disease could be the key to better patient stratification and well-informed patient management either by opting for active surveillance or local salvage for low risk individuals or offering systemic therapy at an earlier time point to a high-risk population [10].

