#### Multi-parametric prostate MRI

A standard prostate mp-MRI protocol as defined by the UK consensus guidelines on prostate MRI [22] will be used to locally stage prostate cancer. Conventional T1 and T2-weighted images of the prostate will be supplemented with diffusion weighted imaging (DWI) MRI (as per hospital site protocol); and +/− dynamic contrast enhanced (DCE) T1-weighted images.

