PSA progression defined as ≥25% and ≥ 2 ng/mL increase in PSA recorded at least 12 weeks from baseline or start of treatment and confirmed on a 2nd reading 3–4 weeks later as previously defined [26, 27].

PSA response defined as ≥50% decline from baseline or start of treatment and confirmed on a 2nd reading 3–4 weeks later [28, 29].

Nodal size change Increase of ≥2 mm and decrease of ≥3 mm in short axis diameter on contrast enhanced mDixon sequence will be considered true change (progression and response respectively) rather than a measurement variation, with a 95% confidence interval. (Based on unpublished data from repeatability studies carried out as part of the LOCATE trial).

Bone lesion (disease progression) ≥ 25% increase in size (sum of short and long axes diameters) of lesions on CT, or MRI [30, 31].

Bone lesion (treatment response) ≥ 50% decrease in size (sum of short and long axes diameters) of lesions on CT/ MRI or normalisation of signal intensity on MRI [30, 31].

Soft tissue lesion size change (disease progression) At least a 20% increase in size of lesion taking as reference the baseline diameter of the lesion [32].

Soft tissue lesion size change (treatment response) at least a 30% decrease in the size of lesion, taking as reference the baseline diameter or disappearance of the lesion [32].

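### Men negative on both baseline tests count as true negatives even with confirmed PSA progression, which can overstate the absolute sensitivity and specificity of WB-MRI

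*Protocol article*

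**What the plan says.** All of this is in the protocol article. Under Derivation of enhanced reference standard, the stated aim for men without metastases on conventional imaging is that "clinical and biochemical follow-up together with changes between baseline and follow-up WB-MRI will be used to enhance the reference standard".

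For men whose baseline WB-MRI is also negative, there are two outcomes:

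- **False negative.** New lesions "coupled with a PSA rise over the 12-month will classify the baseline WB-MRI as false negative, i.e. disease was present but not visualised". Both conditions must be met.
- **True negative.** "Whereas the absence of new lesions regardless of PSA status over the 12-month follow-up period will confer baseline WB-MRI true negative status".

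The unknown class is reserved for conventional-negative men with discordant lesion and PSA changes. The only form of discordance spelled out is "lesion size/number increase without corresponding PSA increase".

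The PSA threshold is explicit: "PSA progression defined as ≥25% and ≥ 2 ng/mL increase in PSA recorded at least 12 weeks from baseline or start of treatment", with a confirmatory second reading. Of the PSA and lesion-size thresholds together the article says "they will be interpreted in the context of treatment intervention and subsequent treatment response or progression".

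The Background states that "up to 50% of men who are considered to be free of metastases by conventional staging methods have micro-metastatic disease", and that biochemical relapse comes on average 7–8 years before metastases are found clinically.

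**The concern.** The label depends on PSA in one direction of discordance and not in the other. A growing lesion without a PSA rise is set aside as unknown. A confirmed PSA rise without a lesion is booked as freedom from nodal and metastatic disease.

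That sits badly with the stated role of biochemical follow-up. In double-negative men without a new lesion, PSA is the one check that does not depend on imaging, and the rule switches it off. What remains is largely the index test itself, repeated at 12 months and read by the same pair of radiologists, with routine imaging as an optional addition.

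It also sits badly with the article's own idea of a false negative, which is disease present but not seen. If occult disease is as common and as slow to appear as the Background says, some of it should lie in exactly this cell.

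The planned outputs are per-patient sensitivity and specificity of WB-MRI, and the economic model is built on the same four outcome classes. A man with missed disease who is labelled true negative leaves the sensitivity denominator and enters the specificity numerator.

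**Working it through.** **Inputs.** The article gives no count of double-negative men with PSA progression and no share of them with metastases, so there is no figure of its own to reproduce here. Sample size gives 130 men at 50% prevalence, that is 130 × 0.50 = 65 with metastases. Every other input below is assumed.

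**Step 1: sensitivity of WB-MRI.** Let u be the number of double-negative men with PSA progression and no new lesion, and f the share of them with nodal or metastatic disease.

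Sensitivity = TP / (TP + FN + f·u)

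Assume TP = 36 and FN = 9. Under the rule as written, sensitivity is 36/45 = 80%. With u = 10:

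| f | Calculation | Sensitivity |
|---|---|---|
| 0 | 36/45 | 80% |
| 0.1 | 36/46 | 78% |
| 0.5 | 36/50 | 72% |
| 1 | 36/55 | 65% |

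**Step 2: both tests, on the scale of the sample size.** Take D = 65 reference-positive men, assumed sensitivities of 0.90 (WB-MRI) and 0.70 (conventional), and m men in the true-negative cell who in fact have metastases. Both tests missed them, so both sensitivities are multiplied by D/(D + m).

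| m | 65/(65 + m) | WB-MRI | Conventional | Difference |
|---|---|---|---|---|
| 0 | 1 | 0.900 | 0.700 | 0.200 |
| 3 | 0.956 | 0.860 | 0.669 | 0.191 |
| 7 | 0.903 | 0.812 | 0.632 | 0.181 |
| 16 | 0.802 | 0.722 | 0.562 | 0.160 |
| 33 | 0.663 | 0.597 | 0.464 | 0.133 |

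The values of m are about 5%, 10%, 25% and 50% of the 65 reference-negative men. The last row is an outer limit. The Background's 50% is an upper figure, and it covers all conventional-negative men, including those whom WB-MRI would detect.

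**Step 3: the paired comparison.** These men are negative on both tests. Moving them to the diseased group adds only to the cell where both tests are negative. The two discordant counts, and so a McNemar test, are unchanged.

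**Step 4: specificity of WB-MRI.** Assume 0.90 among 65 reference-negative men: TN = 58.5, FP = 6.5.

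Specificity = (TN − m) / (TN − m + FP)

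- m = 7: 51.5/58.0 = 0.888
- m = 16: 42.5/49.0 = 0.867
- m = 33: 25.5/32.0 = 0.797

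**Step 5: excluding the group as unknown.** Excluded men leave both margins. In Step 1, sensitivity stays at 36/45 = 80% whatever f is. Specificity falls as in Step 4, with m read as the number excluded.

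**The case against.** The best defence is that PSA does not point to a site. Every man enters with biochemical relapse, the Background says recurrence may be local or distant, and the target condition is nodal and distant disease. A visible lesion is direct evidence of that target and a PSA rise is not. The article also applies this principle against WB-MRI: a baseline lesion that shrinks or resolves without systemic therapy is a false positive whatever the PSA does. This stands. It makes the different treatment of the two discordances defensible in principle, and it shows that the rule is not a device to favour WB-MRI. It does not make a rising PSA uninformative, least of all in a standard that claims to use it.

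A reader might infer that prostate mp-MRI can separate rises explained by local recurrence from unexplained ones. The article does not support that. It describes mp-MRI as standard imaging that "will be used to locally stage prostate cancer" and mentions no repeat at 12 months. A clear baseline scan does not exclude later local recurrence, and a positive one does not rule out coexisting metastases.

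The Discussion concedes that the composite reference standard is a limitation, though not this cell. Figure 2 is not shown and may add detail. Bounding analyses may also sit in an analysis plan that is not shown. The classification rule itself, however, is fixed in the text. The general remark about treatment context does not override its explicit wording.

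**Conclusion.** The point holds as a conditional one. The rule lets missed nodal or metastatic disease be recorded as true negative, and where that happens the absolute sensitivity and specificity of WB-MRI are too high. The size depends on how many double-negative men progress by PSA and what share of them have metastases, and the document gives neither. On the assumed counts, the loss in sensitivity runs from nothing (no such man has metastases) to about 15 percentage points (all 10 do).

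Two stronger readings are tempting and not supported:

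- **That sensitivity is overstated as a matter of fact.** Local recurrence alone can keep PSA rising, so progression without a lesion does not prove a missed metastasis.
- **That the rule gives WB-MRI an edge over conventional imaging in the paired test.** Both sensitivities scale by the same factor and the discordant counts do not move. What is inflated is the absolute level of each and, in proportion, their absolute difference, which is the quantity the sample size targets.

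**What to change.** Flag men who are negative on both baseline tests, have no new lesion at 12 months, and meet the article's own confirmed PSA-progression definition. Report sensitivity and specificity for both tests with this group handled in three ways:

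1. all true negative (the current rule);
2. all false negative;
3. excluded as unknown.

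The third changes specificity only, so relabelling the men as unknown would not by itself answer the concern about sensitivity. The second is needed to show the lower bound.

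Local recurrence on baseline mp-MRI can be shown as a descriptive subgroup but should not decide the label.

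The cost is two extra tabulations from PSA and imaging data that the trial already collects. The downside is a wider and less favourable range around the headline figures. By the Study status section, full analysis had not begun at submission, so the three versions could be specified before the results are known.
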